### Secondary outcomes

The secondary outcomes include the following:Self-Rating Anxiety Scale (SAS) and Self-Rating Depression Scale (SDS) scores at T1, T2, T3, T4, T5, T6, and T7. SAS and SDS developed by Zung will be used to screen for anxious and depressive disorders. The SAS and SDS contain 20 items that cover various anxiety and depression symptoms. Responses are provided on a 4-point scale from 1 to 4 [18, 19];Use of remedial analgesic at T1, T2, T3, T4, T5, T6, and T7The Medical Outcomes Study Health Survey Short Form-36 Item (SF-36) score at T2, T4, T5, T6, and T7. The SF-36 is widely used to assess quality of life in the Medical Outcomes Study. It contains eight domains: physical function; role physical; bodily pain; general health; vitality; social functioning; role emotional; and mental health. Higher scores indicate better health; The incidence of adverse effects (AEs) (after/during/peri-procedural), including hypertension, hypotension, dizziness, nausea, vomiting, numbness of the legs, urinary retention, hematoma, and pain at puncture sites.

### Statistical analysis

Statistical analysis will be performed using SPSS 22.0 (IBM SPSS STATISTICS 22.0) according to the intention-to-treat and per-protocol analyses. The per-protocol set is defined as all patients who have undergone randomization and have received all treatment, except for those who dropped out because of poor efficacy. The Kolmogorov–Smirnov test will be used to evaluate the normality of the data distribution, and Levene’s test will be used to determine the homogeneity of variance. Continuous data will be represented as the mean with SD or median with the interquartile range based on its distribution. The categorical variable will be represented by counts and percentages. The difference between groups will be analyzed by a one-way analysis of variance, Mann–Whitney *U* test, chi-square, or Fisher’s exact tests as appropriate based on the type of variable. Generalized estimating equation analysis will be used for repeated measurement data. Missing data (e.g., loss to follow-up, death, withdrawal) will be updated using the multiple-imputation approach. A two-sided *P* value of 0.05 will be considered statistically significant.

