**Methods:**

This randomized, controlled clinical trial will include 84 patients with pudendal neuralgia who failed to respond to drug or physical therapy. Patients will be randomly assigned into one of the two groups: mono or combined treatment groups. The primary outcome will be a change in pain intensity measured using the visual analog scale. The secondary outcomes will include a Self-Rating Anxiety Scale score, Self-Rating Depression Scale score, the use of oral analgesics, the Medical Outcomes Study Health Survey Short Form-36 Item score, and the occurrence of adverse effects. The study results will be analyzed using intention-to-treat and per-protocol analyses. Primary and secondary outcomes will be evaluated between the mono and combined treatment groups. Subgroup analyses will be conducted based on the initial ailment, age, and baseline pain intensity. The safety of the treatment will be assessed by monitoring adverse events, which will be compared between the two groups.

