### Randomization, concealment, and blinding

Randomly assigned sequences will be generated using SPSS 22.0 (IBM SPSS STATISTICS 22.0) by an independent research assistant, and the results will be sealed in an opaque envelope based on the chief investigator’s instructions. Eligible participants will be randomly assigned to the mono or combined groups at a 1:1 ratio. The allocation will not be revealed until all end point events have been evaluated for the last patient, or severe adverse effects have occurred. The patients and the attending physicians who conduct the treatments will not be blinded to the assigned treatment; however, the outcome assessors and statisticians will be blinded to the group assignments.

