### Primary outcome

The primary outcome will be the VAS score at T1, T2, T3, T4, T5, T6, and T7. The VAS score is a scale consisting of a line, usually 100 mm in length, from “no pain” (score of 0) to “worst imaginable pain” (score of 100).

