### Sample size

According to a previous study, the VAS score was 3.6 ± 1.9 after 1 month of PRF [10]. We assumed that the pudendal nerve PRF with GIB will decrease the VAS score by 30% with a total two-sided type I error rate of 0.05 and a 20% withdrawal rate. A total of 84 patients will be enrolled to achieve a statistical power of 80%.

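### As worded, the per-protocol set drops fully treated patients because treatment failed, so membership depends on the outcome being compared

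*Protocol article*

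**What the plan says.** The Statistical analysis section of the protocol article says that the data will be analysed "according to the intention-to-treat and per-protocol analyses"; the Abstract says the same. It then defines the per-protocol set as "all patients who have undergone randomization and have received all treatment, except for those who dropped out because of poor efficacy". Poor efficacy is not defined there or elsewhere in the article.

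Three other places bear on this definition:

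- Primary outcome: "The primary outcome will be the VAS score at T1, T2, T3, T4, T5, T6, and T7". The outcome is pain intensity, the last visit being 24 weeks after treatment ends.
- Randomization, concealment, and blinding: "The patients and the attending physicians who conduct the treatments will not be blinded to the assigned treatment". Only outcome assessors and statisticians are blinded.
- Intervention: the mono arm has PRF only. The combined arm has PRF and then GIB 3 to 5 days later. Treatment is therefore complete in both arms long before follow-up ends.

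**The concern.** A per-protocol set is meant to describe patients who were treated as the protocol intends. Its membership should rest on eligibility, treatment received and deviations, not on how the patient fared. Here the exception acts after the treatment requirement has been met. Treatment is over within days and follow-up runs for 24 weeks, so most patients who leave for lack of relief will already have received everything assigned. They are adherent failures, and the rule takes them out.

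Two features of this trial add to the exposure. The reason for removal is the same construct as the primary outcome. Patients also know which treatment they had, so the decision to leave, and the reason recorded, may differ between arms. Removing failures makes each arm look better than it was, and the between-arm difference is distorted unless the removals happen to cancel.

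**Working it through.** The plan states no figure for the per-protocol comparison, so there is none to reproduce. The check shows how far the rule could move the result under stated assumptions.

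**Inputs (Sample size section)**

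- Mono arm: "the VAS score was 3.6 ± 1.9 after 1 month of PRF".
- Combined arm: the plan assumes that adding GIB "will decrease the VAS score by 30" per cent. That gives 0.30 × 3.6 = 1.08, a mean of 3.6 − 1.08 = 2.52 and a planned difference of 1.08 points.
- Withdrawal: 20%, all causes, not split by arm or reason.

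**Assumptions (not in the document)**

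- VAS is normal with SD 1.9 in both arms, looked at on one occasion.
- In the first two cases, every patient above a common VAS cut-off c leaves for poor efficacy and is removed.

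**Formula**

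For an arm with mean m, let z = (c − m)/1.9. The mean of those who remain is m − 1.9 × φ(z)/Φ(z), where φ and Φ are the standard normal density and distribution function.

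**Case 1: worst 20% of the mono arm leave**

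- c = 3.6 + 0.8416 × 1.9 = 5.20.
- Mono: 3.6 − 1.9 × 0.2800/0.80 = 2.935.
- Combined: z = (5.20 − 2.52)/1.9 = 1.41, so 7.9% are removed; 2.52 − 1.9 × 0.1476/0.9207 = 2.215.
- Per-protocol difference: 2.935 − 2.215 = 0.72. The ratio to 1.08 is 0.67, a 33% attenuation.

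**Case 2: worst 10% of the mono arm leave**

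- c = 3.6 + 1.2816 × 1.9 = 6.03.
- Mono: 3.6 − 1.9 × 0.1755/0.90 = 3.230.
- Combined: z = 1.85; 2.52 − 1.9 × 0.0721/0.9678 = 2.379.
- Per-protocol difference: 3.230 − 2.379 = 0.851. The ratio is 0.79, a 21% attenuation.

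**Case 3: a softer rule**

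Here only a share q of patients with VAS above 4 leave (simulation, 2 million per arm; the cut-off of 4 and q are assumptions).

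| True difference | q, combined | q, mono | Per-protocol difference (mono − combined) |
|---|---|---|---|
| 1.08 | 0.25 | 0.25 | 1.02 |
| 1.08 | 0.5 | 0.5 | 0.92 |
| 1.08 | 1 | 1 | 0.52 |
| 1.08 | 0.25 | 0.5 | 0.76 |
| 1.08 | 0.5 | 0.25 | 1.19 |
| 0 | equal | equal | 0.00 |
| 0 | 0.25 | 0.5 | −0.26 |
| 0 | 0.5 | 0.25 | +0.26 |

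The row with q = 1 removes 42% of the mono arm, more than double the planned withdrawal, and serves only as a limit.

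**Reading the cases together.** With a real benefit and one rule for both arms, the per-protocol difference is diluted. With no effect and equal dropout, it is unbiased. With unequal dropout, the arm that loses more of its failures gains, whichever arm that is.

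**The case against.** **The sentence may mean the opposite.** The exception could be read as waiving the requirement of full treatment for poor-efficacy dropouts, which would keep them in. This is the less natural reading, but it cannot be ruled out, so nothing firm can be said about intent. The sentence needs rewording either way, because an analyst who follows it as it stands would delete these patients.

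**The damage is confined.** This stands. The question is one of superiority, the exclusion touches only the per-protocol set, and the dilution seen under a common rule does not flatter the combination. Patients with inadequate relief are offered remedial analgesia within the trial (Intervention section), so poor relief need not lead to leaving. Cases 1 and 2 are also deliberately sharp: case 1 turns the whole all-cause withdrawal rate in the mono arm into dropout from the upper VAS tail.

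**Stronger readings that the document does not support.**

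- A reader might infer that the intention-to-treat analysis shares the fault, because "Missing data (e.g., loss to follow-up, death, withdrawal) will be updated using the multiple-imputation approach". The article gives no imputation model. Imputation can condition on a patient's earlier VAS scores, and the model and any sensitivity runs are commonly left to an analysis plan, which is not shown.
- A reader might object that neither set is named as primary. That ranking is also commonly left to the analysis plan.
- A reader might call the treatment requirement unfair, since the combined arm must complete two procedures. That holds for any per-protocol set that compares one step with two, including the one proposed below.
- A reader might expect a large false benefit for the combination. If one arm loses its worst 20%, the other loses none and there is no true effect, a gap of about 0.66 appears (3.6 − 2.935). No document gives dropout by arm, and if the mono arm were the one losing its failures, the gap would favour mono.

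**Conclusion.** The point holds for the per-protocol set. On its plain reading, the definition selects patients on a post-randomisation outcome, in a trial where patients know their treatment. Its size and direction cannot be fixed from the document, which gives no poor-efficacy dropout rate, no split by arm and no definition of poor efficacy. If dropout is driven by VAS with a common cut-off, the planned difference of 1.08 becomes 0.85 when the worst 10% of the mono arm leave. It becomes 0.72 when 20% leave, which is the upper end because 20% is the all-cause rate. Those figures rest on normality, SD 1.9 in both arms and removal strictly by VAS. The intention-to-treat analysis is unaffected by this exclusion, so the matter is one that should be fixed rather than one that undermines the trial's main analysis.

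**What to change.** Delete the exception. Define the per-protocol set as randomised patients who met the eligibility criteria, received the assigned procedure or procedures and had no major protocol deviation. State that patients who stop follow-up because of poor efficacy stay in the set. If the intention was always to retain them, reword the sentence to say so.

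The cost is one or two sentences and an amendment submitted to the institutional review board, as the Ethics and dissemination section requires. No extra data are needed. The change should be made before group assignments are revealed for analysis, since a later change would look driven by the results.

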## Methods

### Study design

This is a multicenter prospective randomized, controlled trial with 1:1 allocation (Fig. 1). It has been registered at www.ChiCTR.org (ChiCTR2200061800). Ethical approval was granted by the Medical Ethics Committee of West China Hospital, Sichuan University. Written informed consent will be obtained from patients or their legal representatives by the designated attending physicians after explaining the trial to patients.

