### Baseline characteristics

The following characteristics will be collected, including demographic characteristics (e.g., initial ailment, sex, age, parity, and history of vaginal delivery), medical history, duration of pain, and baseline score of VAS, SAS, SDS, and SF-36 scores.

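### The plan does not say whether the GEE or unadjusted group tests decide the primary VAS outcome, and states no baseline adjustment for either, although baseline VAS is collected.

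*Protocol article*

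**What the plan says.** In the protocol article's Statistical analysis section, the Kolmogorov–Smirnov "test will be used to evaluate the normality of the data distribution", and Levene's test checks the variances. Then "The difference between groups will be analyzed by a one-way analysis of variance", a Mann–Whitney test, a chi-square test or Fisher's exact test, with the type of variable given as the basis for choosing. The next sentence gives repeated measurements to a GEE. It names no covariates, contrast or time point.

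Under Primary outcome, the outcome is the VAS score at T1 to T7. The abstract describes it differently: "The primary outcome will be a change in pain intensity measured using the visual analog scale". The Baseline characteristics section lists the "baseline score of VAS, SAS, SDS, and SF-36 scores" among the data collected. The abstract also plans a subgroup analysis by baseline pain intensity. No section states that a main comparison is adjusted for a baseline score.

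**The concern.** Two things are left open that the text could settle at once.

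First, two routes to the primary result stand side by side. A one-way ANOVA with two arms is a t test on means, Mann–Whitney compares ranks, and a GEE with an identity link estimates a mean difference. If the deciding analysis is not named, neither is the effect measure. The stated rule, type of variable, cannot separate ANOVA from Mann–Whitney, because VAS is one type of variable. The distribution checks are the only thing in the section that could make that choice.

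Second, a patient's pain before treatment commonly predicts pain afterwards. A comparison without baseline leaves that variation in the error term and leaves chance imbalance between two arms of about 42 uncorrected. Subtracting baseline is not equivalent to adjusting for it: a change score beats the raw score only if the correlation exceeds 0.5, and it does not beat adjustment at any correlation below 1.

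**Working it through.** **Inputs.** From Sample size: "the VAS score was 3.6 ± 1.9 after 1 month of PRF", a 30% lower VAS with combined treatment, "with a total two-sided type I error rate of 0.05 and a 20% withdrawal rate", 80% power and 84 patients. From Study design: 1:1 allocation. The difference is 0.30 × 3.6 = 1.08 on the 0–10 scale that these figures imply. The correlation ρ between baseline and follow-up VAS is not in the document, so it is assumed at 0.3, 0.5 and 0.6.

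**The plan's own figure.** n per arm = 2 × [1.9 × (1.960 + 0.842) / 1.08]² = 48.6, so 49. Allowing for 20% withdrawal, 49 / 0.8 = 61.25, so 62 per arm and 124 in total. The stated 84 is not reproduced. That is a separate matter, used here only to set the evaluable number: 84 × 0.8 = 67.2, or 33.6 per arm, rounded to 34.

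**SD under each analysis.**
- Unadjusted: 1.9.
- Adjusted for baseline: 1.9 × √(1 − ρ²), so the residual variance falls by ρ², that is 9%, 25% and 36%.
- Change score, assuming equal SDs at both times: 1.9 × √(2(1 − ρ)).

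**Power.** Two-sided 0.05, noncentral t, 34 per arm, difference 1.08, one visit:

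| ρ (assumed) | Unadjusted | Adjusted SD | Adjusted power | Change-score SD | Change-score power |
|---|---|---|---|---|---|
| 0.3 | 63.7% | 1.812 | 67.8% | 2.248 | 49.7% |
| 0.5 | 63.7% | 1.645 | 76.0% | 1.900 | 63.7% |
| 0.6 | 63.7% | 1.520 | 82.3% | 1.699 | 73.3% |

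At ρ = 0.3 adjustment gains 67.8 − 63.7 = 4.1 points, while a change score loses 63.7 − 49.7 = 14.0 points.

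**Does choosing the test from the data do harm?** A simulation ran 3,000 trials per scenario with 42 or 34 per arm, on normal data or data truncated to 0–10. A normality test at 0.05 in each arm chose between the t test and Mann–Whitney. Type I error was 4.8–5.3%, against 4.7–5.2% for the t test alone. With normal data, power was 72.7% against 73.3% at 42 per arm and 65.1% against 65.3% at 34 per arm. The error rate and power hardly move. What is lost is an effect measure fixed in advance.

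**The case against.** The strongest reply is that VAS at T1 to T7 is plainly repeated measurement data, so the GEE sentence covers the primary outcome. A GEE is not selected by a normality test, nothing says it is unadjusted, and a covariate list is commonly left to an analysis plan. Much of this stands. It rules out the reading that VAS will be analysed only by unadjusted tests. It does not settle the point, because the article never makes the GEE primary, and the tests it does name for group differences cannot take a covariate.

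Four stronger readings are tempting, and the document does not support them:
- **Baseline VAS is merely descriptive.** The abstract plans a change outcome and a subgroup analysis by baseline pain, so baseline does have a role.
- **The test will switch from visit to visit.** This is an inference. The stated rule is type of variable, and the only wording tied to distribution concerns descriptive summaries. If the GEE is primary, switching does not arise for VAS.
- **The normality pre-test inflates type I error.** The simulation shows no material effect.
- **Centre is wrongly ignored.** The article says "This is a multicenter prospective randomized, controlled trial with 1:1 allocation", but gives no number of centres and does not exclude centre from the model. Silence here is not a decision.

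It is also fair to object that the power figures describe a single-visit comparison, not a GEE over seven visits, and that entry requires VAS of at least 4. That threshold narrows the baseline range and may lower the correlation. Both points stand and limit what the figures can show.

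**Conclusion.** The point holds as a free improvement and a clarification, not as proof that the planned analysis is invalid. The deciding analysis for VAS is not named, the effect measure is therefore open, and no stated analysis adjusts for a baseline score already collected.

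The size is illustrative. For one visit, with the sample size section's own SD and difference and 34 evaluable per arm, adjustment raises power by about 4 points at ρ = 0.3, 12 at 0.5 and 19 at 0.6. The lower figure is the prudent one given the entry threshold. These numbers rest on an assumed correlation and should not be read as the power of the GEE.

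**What to change.** State in Statistical analysis that the primary analysis is one GEE (or linear mixed model) of post-treatment VAS with treatment, visit, treatment-by-visit and baseline VAS. Report the adjusted mean difference with its 95% CI at one time point named in advance. With baseline as covariate, raw score and change give the same treatment estimate, so this also removes the practical consequence of the abstract and the Methods describing the outcome differently; one wording should still be used in both.

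Use the matching baseline score as covariate for SAS, SDS and SF-36. Keep Mann–Whitney as a sensitivity analysis only, and do not let the distribution tests choose the primary analysis. Adjustment for centre is optional and depends on how many centres there are.

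The cost is a few sentences and one degree of freedom for the baseline term. No new data are needed, and the change should be made before outcome data are analysed.

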### Sample size

According to a previous study, the VAS score was 3.6 ± 1.9 after 1 month of PRF [10]. We assumed that the pudendal nerve PRF with GIB will decrease the VAS score by 30% with a total two-sided type I error rate of 0.05 and a 20% withdrawal rate. A total of 84 patients will be enrolled to achieve a statistical power of 80%.

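### The stated inputs require 124 to 126 patients for 80% power; the planned 84 give about 63% after the allowed 20% withdrawal

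*Protocol article*

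**What the plan says.** The whole calculation stands in the protocol article, Methods, Sample size. The control-arm figures come from a cited earlier study, in which "the VAS score was 3.6 ± 1.9 after 1 month of PRF". The treatment assumption and error rates follow: the combination "will decrease the VAS score by 30% with a total two-sided type I error rate of 0.05 and a 20% withdrawal rate". The conclusion is "A total of 84 patients will be enrolled to achieve a statistical power of 80"%.

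Two other sections bear on it. Under Randomization, concealment, and blinding, "Eligible participants will be randomly assigned to the mono or combined groups at a 1:1 ratio". Under Primary outcome, "The primary outcome will be the VAS score at T1, T2, T3, T4, T5, T6, and T7". The Statistical analysis section lists one-way analysis of variance and the Mann–Whitney test among the methods for group differences, and generalized estimating equations for repeated measurements. The Sample size section names no test, and gives no within-patient correlation, no baseline adjustment and no second SD.

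**The concern.** The section prints every input that a two-group comparison of means needs, together with a result those inputs do not produce. The gap is about 40 patients, far beyond rounding or choice of formula.

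Power is the property by which a negative result is judged. A reader who takes 80% at face value will think the chance of missing the assumed effect is 20%. On the plan's own inputs, for a comparison at one visit with the full withdrawal, it is about 37%. A non-significant result would then look like stronger evidence against the combination than it is.

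**Working it through.** **Inputs (Sample size section, except allocation)**

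- Control mean 3.6, SD 1.9, one month after pulsed radiofrequency.
- Reduction with the combination: 30%.
- Two-sided alpha 0.05 (z = 1.960); power 80% (z = 0.842).
- Withdrawal 20%.
- Allocation 1:1 (Randomization section), so 84 means 42 per arm.

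The Primary outcome section defines the VAS as 0 to 100, whereas 3.6 ± 1.9 is evidently on a 0 to 10 scale. Rescaling mean and SD together leaves the standardised difference unchanged, so the calculation is unaffected.

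**Effect size**

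Difference = 0.30 × 3.6 = 1.08. Standardised difference = 1.08 / 1.9 = 0.568.

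**Attempt to reproduce 84**

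n per arm = 2 × (1.960 + 0.842)² / 0.568² = 48.6, so 49. The noncentral t distribution gives power 0.795 at 49 and 0.803 at 50, so the t test needs 50.

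Withdrawal, dividing by 0.8:

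- Normal approximation: 49 / 0.8 = 61.3, so 62 per arm, **124** in total.
- t test: 50 / 0.8 = 62.5, so 63 per arm, **126** in total.

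Other readings that use only the stated inputs, or a common slip in handling them:

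| Reading | Total enrolled |
|---|---|
| No allowance for withdrawal | 98 to 100 |
| Multiply by 1.2 instead of dividing by 0.8 | 118 to 120 |
| One-sided test, divide by 0.8 | 98 |
| One-sided test, multiply by 1.2 | 94 |
| One-sided test, no withdrawal | 78 |
| Combined-arm SD also reduced by 30% (to 1.33), divide by 0.8 | 94 (normal), 96 (t test) |
| Same, multiply by 1.2 (normal) | 90 |
| Same, no withdrawal (normal) | 74 |
| Mann–Whitney efficiency 0.955 | 134 |

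None gives 84. Working backwards, 84 / 2 = 42 = 35 × 1.2, but 35 per arm does not follow from the inputs either: its t-test power is 0.650.

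**Power that 84 does give (t test, difference 1.08, SD 1.9)**

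84 × 0.8 / 2 = 33.6 evaluable per arm.

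| Evaluable per arm | Power |
|---|---|
| 33 | 0.623 |
| 33.6 | 0.631 |
| 34 | 0.637 |
| 42 (nobody lost) | 0.730 |

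The normal approximation gives 0.644 at 33.6 and 0.740 at 42.

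**What would have to be true for 80% power with 84 enrolled and 20% lost**

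At 33 to 34 per arm, the t test needs a standardised difference of 0.690 to 0.700. With SD 1.9 that is 1.31 to 1.33 points, which is 36% to 37% of 3.6 rather than 30%. With a 1.08-point difference it is an SD of 1.54 to 1.57 rather than 1.9.

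**The case against.** The strongest reply is that the primary outcome is VAS at seven visits and the plan names generalized estimating equations for repeated measurements, so a single-visit t test may not be the right yardstick. Suppose the effect is constant over visits, all seven are averaged, and the within-patient correlation ρ is the same for every pair. The variance is then multiplied by (1 + 6ρ)/7. The documents give no ρ, so what follows is a range under assumption. With 33.6 per arm, t-test power is about 86% at ρ = 0.5, 81% at 0.6, 76% at 0.7 and 71% at 0.8. Equivalently, ρ between 0.6 and 0.64 leads to 80 to 86 patients. So a route to roughly 84 exists.

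This shows how the number might be defended; it does not show that the paragraph is right. The section cites one mean and SD at one month and states no correlation, no averaging and no constant effect. The result is also sensitive to ρ, falling below 80% by 0.7. An article may condense a fuller protocol, but condensing does not explain a complete set of inputs printed with an output they do not yield.

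A second reply is that 63% treats every withdrawn patient as contributing nothing. The plan has intention-to-treat analysis with multiple imputation, late leavers supply earlier visits, and fewer than 20% may be missing at one month. That is fair: on the single-visit basis, power lies between 63% (full loss) and 73% (no loss). Even the upper end misses 80%.

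**Conclusion.** The concern holds. On the inputs as printed, the sample size is 124 (normal approximation) to 126 (t test), not 84. With 84 enrolled, power for the assumed 1.08-point difference is about 63% after the planned withdrawal, and 73% if nobody withdraws.

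These figures assume a two-group comparison of means at one visit, a common SD of 1.9, two-sided alpha 0.05 and equal arms. They do not settle the power of a seven-visit model, which depends on a correlation and an effect pattern that the documents do not give. What is established is that the stated 80% does not follow from the stated inputs. Because this concerns the trial's main design claim, it must be corrected.

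**What to change.** Correct the Sample size paragraph in one of these ways:

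- State that 84 patients give about 63% power for a 1.08-point difference (SD 1.9, two-sided 0.05, 20% withdrawal), and 73% without withdrawal.
- State the difference detectable with 80% power under the same conditions, about 1.3 points (36% to 37% of the control mean).
- If 84 came from a repeated-measures calculation, give the analysis, the visits used, the within-patient correlation and its source.

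If the primary analysis were changed to a baseline-adjusted ANCOVA, power should be recomputed with a stated and justified baseline–outcome correlation. For illustration only, 68 evaluable patients give about 76% power at a correlation of 0.5 and about 82% at 0.6; neither value comes from the documents. Recruitment was already under way when the article was submitted, so a correlation should not be chosen to recover 80%.

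The cost is one paragraph. No extra patients are required; the stated power becomes less favourable, and a null result should be read through its confidence interval in that light.
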